## Abstract

**Introduction:**

Individuals with Long Covid represent a new and growing patient population. In England, fewer than 90 Long Covid clinics deliver assessment and treatment informed by NICE guidelines. However, a paucity of clinical trials or longitudinal cohort studies means that the epidemiology, clinical trajectory, healthcare utilisation and effectiveness of current Long Covid care are poorly documented, and that neither evidence-based treatments nor rehabilitation strategies exist. In addition, and in part due to pre-pandemic health inequalities, access to referral and care varies, and patient experience of the Long Covid care pathways can be poor. In a mixed methods study, we therefore aim to: (1) describe the usual healthcare, outcomes and resource utilisation of individuals with Long Covid; (2) assess the extent of inequalities in access to Long Covid care, and specifically to understand Long Covid patients’ experiences of stigma and discrimination.

**Methods and analysis:**

A mixed methods study will address our aims. Qualitative data collection from patients and health professionals will be achieved through surveys, interviews and focus group discussions, to understand their experience and document the function of clinics. A patient cohort study will provide an understanding of outcomes and costs of care. Accessible data will be further analysed to understand the nature of Long Covid, and the care received.

**Ethics and dissemination:**

Ethical approval was obtained from South Central—Berkshire Research Ethics Committee (reference 303958). The dissemination plan will be decided by the patient and public involvement and engagement (PPIE) group members and study Co-Is, but will target 1) policy makers, and those responsible for commissioning and delivering Long Covid services, 2) patients and the public, and 3) academics.

## Introduction

Covid-19 disease results from acute SARS-CoV-2 viral infection. Whilst many patients may remain asymptomatic, or suffer self-limiting disease, symptoms persist in some for an extended period. Long Covid “occurs in individuals with a history of probable or confirmed SARS CoV-2 infection, usually 3 months from the onset of COVID-19 with symptoms, and that last for at least 2 months and cannot be explained by an alternative diagnosis” [1]. It spans multiple healthcare challenges, including physical and psychological symptoms and functional impairment that may be episodic for some and unrelenting for others. It has been estimated that up to 12% of non-hospitalised individuals with COVID-19 may have persistent symptoms for more than 3 months [2]. The nature of the illness, together with its prevalence [3], suggests that Long Covid results in a significant individual, health care system, and societal burden [4–9] which may challenge the delivery of effective, high-quality and sustainable care.

Despite a growing patient population, there is no evidence-based treatment or rehabilitation intervention for Long Covid. Further, non-hospitalised patients and assessments of clinical care pathways have been under-represented in the few Long Covid clinical trials or longitudinal cohort studies so far reported [10]. The epidemiology, clinical trajectory, healthcare utilisation and effectiveness of current care for Long Covid are thus poorly documented [11, 12]. Currently in England, there are fewer than 90 specialist Long Covid clinics in which assessment and treatment is informed by NICE guidelines. However, there is evidence that access to such clinics and related care pathways, the nature of those pathways, and patient experience, varies [13]. Research is thus required to inform diagnosis, care, public health strategies, policy planning, resource allocation and budgeting. It is likewise essential to define the usual care pathway in Long Covid clinics, and to understand patient presentation, and the efficacy and cost of care.

It is important to understand how access to Long Covid services varies, and the barriers to such access and thus to diagnosis and subsequent care. Early evidence suggests that systemic inequalities in referral, assessment and rehabilitation may exist, exacerbated in part by stigma towards specific Long Covid population subgroups, based on demographic or socioeconomic characteristics [7]. It is thus important to document and understand these inequalities and how they relate to pre-pandemic health inequalities, in the new contexts of NHS pressures causing additional pressures on access, such that all patients have access to appropriate care at the right time.

Funded by the National Institute for Health Research (NIHR), the STIMULATE-ICP (Symptoms, Trajectory, Inequalities and Management: Understanding Long-COVID to Address and Transform Existing Integrated Care Pathways) project combines clinical and epidemiological studies; a large randomised controlled trial (RCT) exploring the benefit of an integrated care pathway (ICP) for Long Covid; and mixed methods studies exploring inequalities of care and transferability of the ICP to other long-term conditions (LTCs).

This protocol is for the sub-study, STIMULATE-ICP-CAREINEQUAL, which will provide much needed evidence regarding the nature of usual care, the outcomes such care delivers, costs of such care, and inequalities which currently exist with respect to accessing care. Findings will help inform development and delivery of effective and equitable case identification, support management and treatment for Long Covid.

### Aims and objectives

The aim of STIMULATE-ICP-CAREINEQUAL is to understand current Long Covid care and who is presenting at Long Covid clinics.

Specific objectives are:

To describe usual care, health outcomes and healthcare utilisation of individuals with Long Covid. This will include describing:
Current usual care of Long Covid at each trial site involved in the STIMULATE-ICP RCTThe burden of illness at presentation to Long Covid clinicsPatient outcomes from current care pathwaysResource utilisation and the cost of current care at the patient and service levelTo assess the extent of inequalities in access to Long Covid care. This will include describing:
Whether patients who are currently accessing Long Covid services are representative of the overall population of people living with Long Covid, and if there are inequalities in access to care and outcomes.The barriers and facilitators to accessing Long Covid diagnosis, care and supportThe nature and extent of stigma and discrimination experienced by Long Covid patients.

## Materials and methods

In order to collect and analyse data in the most pragmatic and effective and timely manner, we opted for a mixed methods approach to address these research questions. An overview of the research components, data collection methods and analyses are set out in Fig 1. Patients and health professionals will be interviewed to understand their experience and document how the clinics function, while patient data from Long Covid clinics will be explored to understand the nature of Long Covid and the care received. A follow up survey of patients will provide an understanding of the outcomes of care and the cost.

**Fig 1 pone.0271978.g001:**
[figure not shown]
Study design for the CARE-INEQUAL work package for STIMULATE-ICP.

### Qualitative methods

#### Design

Qualitative methods will be used to understand current care pathways, patient and clinician experience of Long Covid services, and barriers and facilitators to care access. The four research components included are:

a) **Current care pathways at the 6 initial sites included in the STIMULATE-ICP clinical trial:** The service manager and/or clinical lead for each Long Covid clinic will be asked to complete a structured survey to collect key information related to the clinic set up and patient pathways. The survey will be followed with semi-structured interviews with the service manager and clinical lead to clarify any outstanding queries, and to understand their perception of the effectiveness of services and the sustainability of the clinics.b) **Patient experience of current Long Covid care:** Both discharged and current patients will be invited to participate in either interviews (6 sites, n = 4 at each site) or focus groups (1 at each of the 6 sites, n = 6–8). They will be asked to describe their experience of care, including referral, assessment, diagnosis and treatment. This will provide an understanding of the patients’ perception of Long Covid care including any barriers to accessing care, their experience of the care pathway and any outcomes they experienced as a result of treatment.c) **Patient experience of engagement with Long Covid care and stigma**: Semi-structured interviews will be carried out with Long Covid patients who have been referred to or accessed NHS Long Covid services (n = 25–50). Patients will be asked to share their experiences of barriers and facilitators when accessing care. Interviews with people living with Long Covid but not accessing care will take place in a later phase of the study. This will be set out in a separate future protocol.d) **Clinician experience of current Long Covid care:** Semi-structured interviews will be undertaken with health care professionals working in Long Covid clinics (6 sites, n = 4 at each site), to explore their experiences of joining and working within the clinic, and their perception of inequalities in access to care for Long Covid patients. Participants will be recruited from four professional groups nominated by each site, to reflect the plurality of service design.

#### Data analysis

Interviews and focus groups will be carried out remotely using an online platform and will be recorded and stored securely. The data will be transcribed using a GDPR compliant transcribing company and will be anonymised and checked for accuracy. The data will be subject to thematic analysis, following Braun and Clarke’s thematic analysis framework [14] and using NVivo12 software.

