### Ethics

Ethical approval for the project has been granted by the Berkshire Research Ethics Committee and the NHS HRA, REC reference: 22/SC/0047.

We will obtain written consent from participants for interviews and focus groups. Consent will be sought for prospective and retrospective data collection as part of the cohort study. Electronic consent will be used for the questionnaire and data access.

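### Online is the only mode stated for the patient interviews and focus groups on barriers to care, so patients with poor digital access risk being under-represented

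*Protocol article*

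**What the plan says.** The mode is fixed in one sentence of the Data analysis section under Qualitative methods: "Interviews and focus groups will be carried out remotely using an online platform and will be recorded and stored securely". It carries no exception and makes no distinction between components.

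Two of the components it covers collect patients' accounts of access:

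- **Component (b)**, on experience of current care: "Both discharged and current patients will be invited to participate in either interviews" or focus groups. The plan is 4 interviews and one focus group of 6 to 8 people at each of 6 sites. Barriers to access are among the matters it is meant to illuminate.
- **Component (c)**, on engagement and stigma: "Semi-structured interviews will be carried out with Long Covid patients who have been referred to or accessed NHS Long Covid services", with 25 to 50 participants. The topic is explicit: "Patients will be asked to share their experiences of barriers and facilitators when accessing care".

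Both serve a specific objective under Aims and objectives, which begins "The barriers and facilitators to accessing Long Covid diagnosis, care and" and ends with support. The Introduction gives the motive, namely early evidence that "systemic inequalities in referral, assessment and rehabilitation may exist".

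People outside services are left for later: "Interviews with people living with Long Covid but not accessing care will take place in a later phase of the study", under a separate protocol. On consent, the Ethics section says: "We will obtain written consent from participants for interviews and focus groups". It names electronic consent only for the questionnaire and data access.

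**The concern.** The mode of data collection may select on something the component is meant to study. A patient who lacks a suitable device, a reliable connection or confidence with online tools may find it hard to join an online interview. The same patient may, for the same reasons, have found it hard to obtain referral, assessment or follow-up. If such patients take part less often, barriers of this kind will be reported less often than they occur.

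This matters more in a thematic analysis than in a survey. A survey that under-samples a group can sometimes be reweighted. A theme that would have come from the accounts of people who were not interviewed cannot be recovered at the analysis stage. The inequality objective is where the gap would be felt.

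**Working it through.** No power, error-rate or sample-size figure is involved, and the plan states none on this point. The check is a comparison of sections, followed by a count of the places affected.

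**Step 1. Is any other mode stated?** No. The Design section under Qualitative methods says who is invited and what they are asked, and nothing on mode. The Ethics section covers consent. The Discussion names recruitment as a possible challenge, but links it to the variety of sites. No telephone, face-to-face or assisted route appears, and digital exclusion is not listed as a limitation.

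**Step 2. Does eligibility mention digital access?** No. Component (c) asks only that patients have been referred to or have used NHS Long Covid services. Component (b) takes discharged and current patients. Ability to use the platform is therefore a practical condition set by the mode, not a stated criterion.

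**Step 3. Could another component supply the missing accounts?**

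| Source | What it gives | Does it replace the patient's own account? |
|---|---|---|
| (d) clinician interviews | Clinicians' perception of inequalities in access | No, it is second-hand |
| (i) routine clinic data against national survey data | Who is under-represented in services | No. It does not depend on online participation, but it shows who and not why, and digital access is not among the listed variables |
| (e) and (f) follow-up questionnaire | Symptoms, outcomes, stigma | No. It is not described as asking about access barriers, and its consent is electronic |
| Later interviews with people not accessing care | A different population | Not part of this protocol |

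**Step 4. How many patient places fall under the stated mode?**

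- (b) interviews: 6 × 4 = 24
- (b) focus groups: 6 × 6 = 36 to 6 × 8 = 48
- (c) interviews: 25 to 50
- Total: 24 + 36 + 25 = 85 to 24 + 48 + 50 = 122
- Individual interviews alone: 24 + 25 = 49 to 24 + 50 = 74

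Staff interviews in (a) and (d) use the same mode but are not plausibly affected.

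**Step 5. How many patients might be concerned?** The article gives no share of clinic patients who cannot take part online. As an illustration only, assume a share of 5% to 20%, and a sample that mirrors the clinic population. The expected number is places × share:

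- All of (b) and (c): 85 × 0.05 = 4.3 to 122 × 0.20 = 24.4
- Component (c) alone: 25 × 0.05 = 1.3 to 50 × 0.20 = 10

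These are the numbers such patients would contribute if mode were no obstacle. They do not estimate how many will be lost. That depends on arrangements the article does not describe.

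**The case against.** The strongest reply is that this is one sentence on logistics in a condensed article. It does not say that online is the sole mode, sets no digital-access condition, and does not rule out dial-in or assisted participation. Individual adjustments commonly sit in the full protocol or the invitation, neither of which is shown. This stands in part. It defeats any claim that exclusion is certain. It does not dispose of the point, because the article is not silent on mode: it states one, without exception, for components whose subject is access.

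A reader might go further and infer several things that the document does not support:

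- *That digitally excluded patients will be removed, so that none will take part.* This assumes that no accommodation exists, and the article does not establish that.
- *That sessions are by video, which some patients could not tolerate.* The article says only that there is an online platform and a recording.
- *That recruitment itself is digital.* How patients are approached for (b) and (c) is not described, and consent for interviews is written.
- *That the sample is purposive, or that a missing theme will be taken as evidence that a barrier is absent.* Neither is stated.

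Two further replies have force. Remote participation spares travel, which may help patients with fatigue or functional impairment, so the mode may widen participation for some. And telephone would not clearly solve fatigue, cognitive symptoms or lack of a private space. The point is therefore confined to device, connection and digital confidence. Patient and public members informed the approach to interviews, which counts in favour of the design but does not show that this question was settled.

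Finally, (d) and (i) give other evidence on inequality, so the objective as a whole does not rest on the patient interviews. What remains is the gap in patients' own accounts.

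**Conclusion.** The point holds as a risk of under-representation in patient components (b) and (c). Online is the only mode stated, it is stated without exception, and it bears on a characteristic that may itself be a barrier to care. Nothing else in this protocol supplies those patients' own accounts.

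The conclusion rests on two assumptions: that the sentence is followed as written, and that some eligible patients lack a device, a connection or digital confidence. The size of the loss cannot be derived. The 5% to 20% range is illustrative and has no source in the document.

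The document does not support saying that these patients are shut out, or that the inequality objective fails. Remote interviewing is a defensible choice. The matter is a cheap improvement.

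**What to change.** Amend the sentence on mode in the Data analysis section under Qualitative methods as follows:

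1. Individual patient interviews in (b) and (c) are offered online or by telephone, at the participant's choice.
2. The invitation names the telephone option, and telephone interviews are audio-recorded, stored and transcribed under the same arrangements.
3. Focus groups stay online, and anyone who cannot join one is offered a telephone interview.
4. The mode used is recorded for each participant and reported with the findings.

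If the full protocol already provides a non-digital route, it is enough to state it here and to add the recording and reporting of mode. No quota of telephone places is needed.

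The cost is a short amendment to the protocol and invitation, with the same interviewers, topic guide and transcription. The downside is the loss of visual cues by telephone.

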### Cohort study and analysis of accessible data

#### Design

To explore the effectiveness of current Long Covid care, we will recruit to a cohort study those patients from sites which collected health outcome measures at the initial assessment as part of routine care. Patients at different points in their Long Covid pathway will be invited to complete health and wellbeing questionnaires they completed earlier in their care pathways.

e) **Cohort study—existing data and extended questionnaire**: Patients at a minimum of one site (confirmed as University College London Hospitals NHS Trust, UCLH, and further sites will be identified in the initial site survey detailed in part (a) above) will be invited to participate in a cohort study, including analysis of their retrospective data, and completion of an extended questionnaire. At their initial clinic assessment, patients will be asked to complete a survey of their symptom nature and duration, and outcome measures. This study will aim to collect follow-up data on these measures to evaluate the extent of recovery in clinical and quality of life outcomes including: symptoms and employment status will be documented, and health and symptoms explored though the EQ-5D-5L questionnaire, Fatigue Assessment Scale (FAS), 2-item Patient Health Questionnaire (PHQ-2), and 2-item Generalised Anxiety Disorder (GAD-2) scale. Some additional questions will be asked in the follow-up questionnaire, including additional symptoms and whether symptoms have resolved, as well as asking patients to complete the Work and Social Adjustment Scale (WSAS) and the Perceived Deficits Questionnaire (PDQ5) (outcome measures included in the STIMULATE-ICP RCT).f) **Assessment of Long Covid stigma:** No validated Long Covid stigma scales currently exist. The one used for this study has been developed based on health stigma theory and emerging qualitative evidence of Long Covid stigma. It utilises items from existing scales related to stigmatising conditions (myalgic encephalomyelitis (ME)/chronic fatigue syndrome (CFS), depression and HIV). These items were reviewed by people living with Long Covid both internal (our patient and public involvement and engagement (PPIE) collaborators) and external to this study. As part of the Long Covid follow-up questionnaire in part (e), patients will be asked to complete a stigma questionnaire. This will be analysed along with other routine data to determine the prevalence and correlates of stigma and discrimination.

Additional data will be requested from the clinics, NHS England, NHS Digital and the Office for National Statistics (ONS) in order to:

g) **Describe the Long Covid patient population:** Accessible patient data, such as those from the primary care electronic health record, will be analysed to understand the patient population in terms of age, gender, ethnicity, sociodemographic status, health care resource use, clinical and health outcomes.h) **Estimate the resource use and cost of care:** Patient reported data on resource use, costs and time of work, will be valued using published NHS costs (National Reference Costs; PSSRU Unit Costs of Health and Social Care) and other standard reference costs to estimate the overall societal costs of Long Covid care. Additionally, we will use clinic data collected in part (a) to calculate the costs of delivering care in Long Covid clinics and analyse how this varies by clinic and patient demographics.i) **Examine inequalities in Long Covid care:** Routinely collected socio-economic, demographic and health characteristics of patients accessing services will be compared to Office for National Statistics (ONS) data on COVID-19 infections and Long Covid in the community, to estimate representativeness of those reaching Long Covid services.

#### Data analysis—Components (e), (g) and (h)

We will use statistical analysis and health economic methods to understand the associations between different symptoms, risk factors and Long Covid outcomes. We will investigate frequencies and the predictive value of different investigations and procedures employed in the assessment of patients referred to Long Covid clinics. We will study community, primary and secondary care healthcare utilisation in individuals with Long Covid at the different stages of diagnosis, treatment and management. We will also consider any confounding effect of comorbidities and multimorbidity by including them as covariates in regression analyses.

Data will be analysed to evaluate the extent of improvement in symptoms and health outcomes over time using appropriate methods, including t-tests and ANOVA. This will include, specifically, longitudinal change in EQ-5D-5L (including the accompanying visual analogue scale, EQ-VAS), employment status, FAS, PHQ-2, GAD-2 scales and resolution of previous symptoms. An evaluation of the extent of healthcare utilisation through the care pathway will be made.

Published costs will be applied to resource use to estimate the cost of Long Covid care. Combining the information on the Long Covid clinic provision with what it costs to deliver care at a patient level and estimates of the number of patients who will need Long Covid care, we will calculate the total cost of delivering care in Long Covid clinics in England over one year. In addition, we will describe the distribution of costs across primary and secondary care and the proportion of cost associated with diagnosis, pharmacological and non-pharmacological treatments including physical rehabilitation and counselling.

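### Follow-up length varies by design, but the methods named for improvement over time do not use elapsed time, so the mean change has no defined horizon and subgroup comparisons may be confounded

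*Protocol article*

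**What the plan says.** The Design text under 'Cohort study and analysis of accessible data' sets up a repeat measurement without a fixed interval: "Patients at different points in their Long Covid pathway will be invited to complete health and wellbeing questionnaires they completed earlier in their care pathways". Component (e) places the first measurement at clinic entry: "At their initial clinic assessment, patients will be asked to complete a survey of their symptom nature and duration, and outcome measures". It gives the purpose of the second: "This study will aim to collect follow-up data on these measures to evaluate the extent of recovery in clinical and quality of life outcomes". No follow-up time or window is attached to it.

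'Data analysis—Components (e), (g) and (h)' states that the data will be analysed "to evaluate the extent of improvement in symptoms and health outcomes over time using appropriate methods, including t-tests and ANOVA", and lists the outcomes as "longitudinal change in EQ-5D-5L (including the accompanying visual analogue scale, EQ-VAS), employment status, FAS, PHQ-2, GAD-2 scales and resolution of previous symptoms". The adjustment named there is: "We will also consider any confounding effect of comorbidities and multimorbidity by including them as covariates in regression analyses". Time since assessment is not mentioned as a covariate or stratifier.

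'Data analysis—Components (f) and (i)' adds that demographic and socioeconomic predictors of clinical outcomes will be explored. Follow-up time is not among the variables listed there either.

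**The concern.** A before-and-after change is interpretable only with the time over which it occurred. Here that time differs between patients by design, and a t-test or ANOVA on the change averages over it. Two studies of the same illness would report different mean improvement simply because their questionnaires reached patients earlier or later.

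The second consequence concerns comparisons. The study asks whether outcomes are unequal between groups. If one group has been followed for longer, and outcomes move with time, part of any difference in recovery reflects the calendar. The article gives reasons to think this could happen. Its Discussion says the participating services differ in how long they have been running, and it reports waiting lists and temporary closures in some areas. Its Introduction suspects unequal referral between population subgroups. Timing may therefore be linked to the characteristics under study.

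**Working it through.** **Nothing to reproduce.** The article states no sample size, SD, effect size or follow-up interval for the cohort. All inputs below are assumptions, chosen to show direction and range.

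**Check 1: does the pooled mean depend on survey timing?** Assume recovery, in SD units, of 0.5 × (1 − exp(−t/6)), with t in months since assessment. For follow-up uniform between a and b, the mean is 0.5 × {1 − [6/(b − a)] × [exp(−a/6) − exp(−b/6)]}.

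- 1–6 months: 0.5 × {1 − (6/5)(0.8465 − 0.3679)} = 0.21 SD
- 3–12 months: 0.5 × {1 − (6/9)(0.6065 − 0.1353)} = 0.34 SD
- 6–18 months: 0.5 × {1 − (6/12)(0.3679 − 0.0498)} = 0.42 SD
- 1–24 months: 0.5 × {1 − (6/23)(0.8465 − 0.0183)} = 0.39 SD

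One recovery curve thus yields 0.21 to 0.42 SD, a twofold range, depending only on when people are surveyed.

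**Check 2: what happens to a subgroup comparison?** Both groups follow the same trajectory: change = slope × t + error, with error SD 1 and slope 0.03 or 0.05 SD per month. Follow-up is uniform over 10 months, centred at 8 months in one group and at 8 months plus a gap in the other. There are 100 or 200 patients per group and 4,000 runs. A two-sample t-test on change at a nominal 5% rejects in:

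| Gap in mean follow-up | n = 100, slope 0.03 | n = 100, slope 0.05 | n = 200, slope 0.03 | n = 200, slope 0.05 |
|---|---|---|---|---|
| 0 months | 5.2% | 5.2% | 5.7% | 5.4% |
| 2 months | 7.4% | 10.4% | 9.9% | 17.0% |
| 4 months | 14.2% | 28.3% | 22.1% | 50.5% |
| 6 months | 23.5% | 55.8% | 43.4% | 83.8% |

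The expected spurious difference is gap × slope, from 2 × 0.03 = 0.06 SD to 6 × 0.05 = 0.30 SD. Hand check of the last cell: SD = √(1 + 0.05² × 100/12) = 1.010; SE = 1.010 × √(2/200) = 0.101; 0.30/0.101 = 2.97; Φ(2.97 − 1.96) = 0.84, which agrees.

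With elapsed time added as a covariate, the rejection rate is 4.3% to 6.0% in every scenario. The time term is linear here and so is the assumed trajectory; if real recovery is curved, the time term must be flexible enough to follow it.

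**Check 3: a curved trajectory.** Take 0.8 × (1 − exp(−t/9)), 100 per group and change SD 1. Follow-up of 1–8 months gives a mean gain of 0.30 SD and 6–14 months gives 0.53 SD, so the t-test rejects in about 36% of studies. If the windows are offset by only one month (1–8 v 2–9), the figure is about 7%; by two months, about 11%. The problem scales with the imbalance and vanishes without it.

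**The case against.** The strongest reply is that the method list is open. The article speaks of appropriate methods and gives t-tests and ANOVA as examples, names no main analysis, and plans regression with covariates in the same section. A full protocol or analysis plan may hold the time terms. This stands in part: the article does not rule out a time-adjusted model. But it does choose to name methods for change over time and covariates for regression, and neither takes up the varying follow-up that its own design creates.

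A second reply is that a paired t-test on within-patient change is valid. That is correct, as a test of average change over the realised mix of intervals. It does not supply a horizon.

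Several stronger readings are tempting, and the text does not support them:

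- **That intervals vary widely.** The article says only that patients are at different points; it gives no spread.
- **That subgroup comparisons are confounded.** This needs follow-up length to differ by subgroup and outcomes to change with time. Both are plausible, neither is stated, and the use of ANOVA to compare subgroups is itself an inference. Only one cohort site is confirmed, so differences between clinics arise only if others join.
- **That an unpaired test is planned.** The article speaks of longitudinal change on repeated measures in the same patients, which implies pairing.
- **That employment status and symptom resolution will be t-tested.** The open wording leaves room for categorical methods, and the section on components (f) and (i) names chi-square tests and logistic regression where they apply.
- **That respondents should be weighted for non-response.** The Ethics section makes cohort data depend on consent, so baseline data on non-responders may be unavailable. Such weighting is also commonly left to an analysis plan.

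**Conclusion.** The point holds in a limited form. Unequal follow-up is built into the cohort, and the methods and covariates named for improvement over time make no use of elapsed time. As written, the mean change has no defined time horizon. Confounding of subgroup or clinic comparisons is a conditional risk, not an established fact.

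Its size cannot be fixed from the article. Under the assumptions shown, the pooled change moves between 0.21 and 0.42 SD with survey timing alone. False-positive rates are about 7–17% for a 2-month gap in mean follow-up and 24–84% for a 6-month gap, against 4–6% after adjustment for time. With equal follow-up across groups there is no inflation. The study is descriptive and states no confirmatory test, so the harm is misreading of recovery and of inequality in recovery, not a failed trial. The correction is cheap enough to be worth making.

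**What to change.** In 'Data analysis—Components (e), (g) and (h)':

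- Make the main analysis of EQ-5D-5L, EQ-VAS, FAS, PHQ-2 and GAD-2 a regression or mixed model with baseline score and time since initial assessment, plus clinic if more than one site joins. Allow a non-linear time term where the data support it.
- Report estimated change with 95% CI at stated times, chosen in advance. A paired test may stay as a descriptive summary, labelled as average change over the observed intervals.
- Report the distribution of the assessment-to-survey interval, overall and by subgroup.
- Put the same time term in the models for employment status and symptom resolution.

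In 'Data analysis—Components (f) and (i)', add time since initial assessment to the analysis of demographic and socioeconomic predictors of clinical outcomes.

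The cost is slightly more analysis work, and confirming that the dates of clinic assessment and questionnaire completion are both captured. The article does not say that they are.
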